## Methods

### Study Design

This is a 2-arm, parallel-group pseudorandomized controlled trial that will be performed at 3 sites—Greece, Ukraine, and Kazakhstan—and will include the evaluation of the educational VP interventions. This will be conducted in 2 axes that correspond to the primary outcomes of the study. The first axis aims to determine the efficacy of the educational VP interventions, while the other will involve assessing the acceptance and opinions of the participants about the VP modality for education and information purposes. Correspondingly, the primary outcomes of the study include the efficacy and the acceptance of the VP interventions, and the secondary outcomes include the opinions of the participants about the VP modality for education and information purposes. The aims of the study are summarized in the following research question: are patients with AF better educated about their post–acute phase lifestyle changes and needs by using mobile virtual scenarios compared to conventional patient education methods?

Α prepilot arm of the study will be initially conducted in Greece and will consist of hospitalized patients due to AF episodes, all of which should complete a short quiz. From among the patients who complete the quiz, half of the patients will be randomly allocated to the control (normal clinical information) cohort, while the other half will be informed with the help of VP vignettes.

After the prepilot arm, the pseudorandomized controlled trial will be conducted multicentrically. The same process, as in the prepilot arm, will be followed for recruiting the core sample, exploring the efficacy and impact of VPs in educating patients with AF. Since this trial will have been conducted during the COVID-19 pandemic, all national and international health and safety protocols will be followed.

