### Intervention Cohorts

The full pilot arm of the study will be conducted multinationally in Greece, Ukraine, and Kazakhstan (Figure 1). In Greece, a pool of 700 patients will be reached by phone, and they will participate in the trial from their home. From among the patients contacted remotely, and from those who respond, those who would be eligible will be asked to complete the intervention. From among the patients who choose to complete the quiz, half of them will be randomly allocated to the control (normal clinical information) cohort, while the other half will be informed with the help of VP vignettes. In Ukraine, 160 patients will be reached and will be divided into the control and intervention groups. Finally, at the Kazakhstan center, 190 patients will be contacted.

Given that all recruitment and adherence criteria are followed, sufficient sample sizes for control and intervention groups will be ensured so as to use the Welch *t* test for analysis, which is robust to large sample size inequalities, in order to not exclude any useful data from the generalized multicenter VP cohort.

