### Blinding (Masking)

Participants and trial personnel will not be blinded after the point of assignment to interventions because of the nature of the interventions and outcomes assessed. Participants will know which group they will belong to because the group-specific intervention will follow immediately after randomization.

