### Evaluation Design

#### Evaluation Instruments

For educational efficacy, a multiple-choice questionnaire (MCQ) for knowledge retention will be used (Textbox 2). The choice of questions was based on the European Society of Cardiology’s *Guidelines for Management of Atrial Fibrillation* [29]. This instrument will be translated for all participating centers in Greece, Ukraine, and Kazakhstan. The translation and evaluation of the translation will be performed by teams of bilingual experts. The instrument in its original version will be provided to bilingual persons in alternating language order and will be assessed accordingly. Scoring each questionnaire follows a simple process of allocating a numerical score equal to the number of choices in the MCQ to weigh each response for randomly selecting the correct question. For example, a question that has 4 possible responses in the MCQ will be scored 4 points if answered correctly, while a question that has 5 possible answers will be scored with 5 points if correctly answered.

Questionnaire for knowledge retention on atrial fibrillation (the asterisk indicates the correct answer).

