## Results

The trials will start in 2024 and are expected to end later that year or in early 2025 or when the needed sample size is achieved. The initial results are expected by March 2024.

To assess the results from the prepilot evaluation questionnaires, the Welch *t* test will be conducted. Of note, we decided to conduct the Welch *t* test because some of our sample sizes will be heavily unequal between intervention and control groups. The standard Student *t* test is robust to inhomogeneity of variance when sample sizes between cohorts are the same; however, this is not true for largely differing cohort sample sizes. The Welch *t* test does not assume homogeneity of variance and, hence, is robust to widely varying sample sizes [30,31].

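### The only quiz placed in time comes before allocation and education; the article never says when the efficacy MCQ follows education, whether it is that quiz, or which score the Welch t test compares

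*Protocol article*

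**What the plan says.** Four parts of the protocol article bear on when knowledge is measured and how it is compared.

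- **Order in the prepilot (Study Design).** Hospitalized Greek patients complete a short quiz, and then: "From among the patients who complete the quiz, half of the patients will be randomly allocated to the control (normal clinical information) cohort". For the multicenter trial, "The same process, as in the prepilot arm, will be followed for recruiting the core sample".
- **Order in the main Greek trial (Intervention Cohorts).** "From among the patients who choose to complete the quiz, half of them will be randomly allocated to the control (normal clinical information) cohort".
- **Timing of the education (Blinding).** "the group-specific intervention will follow immediately after randomization".
- **Outcome instrument (Evaluation Instruments).** "For educational efficacy, a multiple-choice questionnaire (MCQ) for knowledge retention will be used". The ten items and the scoring are given. The time of administration is not, and the section does not link this MCQ to the quiz used at recruitment.

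The analysis is a Welch t test between groups. Results introduces it with the words "To assess the results from the prepilot evaluation questionnaires", and Intervention Cohorts names it for the multicenter comparison. Neither place says whether it is applied to a post-education score or to a change.

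Allocation differs by site (Inclusion and Exclusion Criteria and the Recruitment Process). It is random in Greece, by convenience and mostly to VP in Ukraine, and entirely to VP in Kazakhstan. The multisite comparison sets all VP patients against the Greek and Ukrainian controls.

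**The concern.** The stated order is quiz, allocation, education. The Discussion says the aim is to show knowledge transferred to the learner and retained, which needs a measurement after education. The visible text contains none that is common to both arms. The questions inside the VP case belong to that arm alone and cannot serve as a comparative outcome.

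Two consequences follow, depending on what the quiz is.

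- If the quiz score is the analysed score, the randomized Greek comparison contrasts two groups that have not yet been treated differently.
- If the quiz is a baseline, nothing says how it enters the analysis. In Greece this is a matter of precision. In Ukraine and in the pooled comparison, where arms are not formed by chance, initial knowledge may differ between arms and a score taken before education is the obvious protection.

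A claim of retention also needs a stated interval between education and test, and none is given.

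**Working it through.** The article gives no alpha, power, SD, effect size or calculated sample size, so there is no figure of its own to reproduce. The first step compares the text; the rest is illustration on labelled assumptions.

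**1. Sequence.** Study Design and Intervention Cohorts both select patients for allocation from quiz completers. Blinding puts the intervention straight after randomization. The quiz therefore precedes education in the Greek prepilot and the main Greek trial. Evaluation Instruments gives the MCQ no time. No visible section states a knowledge test after education.

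**2. If the pre-allocation score were the outcome (Greece).** Both arms are random halves of the same untreated group. The expected difference is zero whatever the education does, and the rejection rate equals alpha.

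**3. If the quiz is a baseline (Greece).** Assume two-sided 5%, 80% power, equal arms and pre/post correlation r. Relative to comparing post-education scores alone, the variance is 2(1 − r) for a change score and 1 − r² for regression on the baseline. Patients per arm for an assumed 0.3 SD difference:

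| r (assumed) | Variance, change | Variance, adjusted | n post-only | n change | n adjusted |
|---|---|---|---|---|---|
| 0.3 | 1.40 | 0.91 | 175 | 245 | 159 |
| 0.5 | 1.00 | 0.75 | 175 | 175 | 131 |
| 0.7 | 0.60 | 0.51 | 175 | 105 | 89 |

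Greece contacts 700. If half take part (assumed), each arm has 700 × 0.5 / 2 = 175. The detectable difference is 2.802 × √(2/175) = 0.30 SD post-only. With adjustment at r = 0.5 it is 0.30 × √0.75 = 0.26 SD.

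**4. Pooled comparison.** Inputs from Intervention Cohorts: 700, 160 and 190 patients contacted. Assumptions: equal response at all sites; 60% to 90% of Ukrainian patients on VP; initial knowledge in Kazakhstan 0.5 SD away from the other sites, carried through to the analysed score; no true effect; normal approximation.

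- 60% in Ukraine: VP = 350 + 96 + 190 = 636 and control = 350 + 64 = 414. Kazakhstan is 190/636 = 29.9% of VP and 0% of control. Shift = 0.5 × 0.299 = 0.149 SD.
- 90% in Ukraine: VP = 350 + 144 + 190 = 684 and control = 350 + 16 = 366. Kazakhstan is 190/684 = 27.8% of VP. Shift = 0.5 × 0.278 = 0.139 SD.

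With SE = √(1/n control + 1/n VP) in SD units, the two-sided 5% test rejects with these probabilities:

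| Response at every site (assumed) | Rejection probability, no true effect |
|---|---|
| 100% | 0.57 to 0.66 |
| 50% | 0.33 to 0.39 |
| 25% | 0.19 to 0.22 |

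The Welch form guards against unequal variances, not against a difference in starting knowledge.

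**The case against.** The best defence is that an article condenses a fuller protocol, and that the analysed score and covariates are usually left to the analysis plan. The Discussion plainly intends a measurement after education, and the flowchart, which is not visible here, might show one. Much of this stands, and it rules out several stronger readings that a reader might infer.

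- **That the outcome is definitely measured before the intervention.** The article never says the quiz and the MCQ are the same instrument. The quiz could be a screen, a baseline or the MCQ itself.
- **That the plan discards its baseline.** The Welch test is named without its input. A Welch test on change scores would use a pre-score and is not excluded.
- **That every site tests before allocating.** The order is explicit only for Greece. The prepilot process is carried over for recruitment, and the Ukrainian and Kazakh descriptions mention no quiz.
- **That a post-only Welch test would be invalid in Greece.** Under randomization it is valid, only less precise.
- **That the MCQ is taken at the same contact as the education.** Its timing is unstated, so it cannot be called immediate.

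The defence does not remove the defect. The timing of a primary outcome is part of the design, and an analysis plan cannot supply a post-test that the visit sequence lacks. The article also does more than stay silent: it twice puts its only timed quiz where that quiz cannot measure the effect of education.

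**Conclusion.** The point holds as an unresolved conflict between the stated sequence and the stated purpose. Followed literally, the Greek trial measures knowledge before education and could not show efficacy. On the more sensible reading, the pre-allocation quiz is a baseline with no stated role.

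In Greece the cost of leaving it out is precision: adjusted variance is 0.91, 0.75 or 0.51 of post-only variance at assumed correlations of 0.3, 0.5 or 0.7. The larger exposure is bias in the non-random Ukrainian and pooled comparisons. For the pooled contrast the illustration gives a shift of 0.14 to 0.15 SD, which rests wholly on an assumed 0.5 SD difference in Kazakhstan and on equal response across sites. The documents support neither a claim that such a difference exists nor a claim that the baseline will certainly go unused.

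**What to change.** Reconcile Study Design, Intervention Cohorts, Evaluation Instruments and Results as follows.

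1. State that the same MCQ is given before allocation and again after the VP case or the dictated information, at one fixed interval identical in both arms and at all sites. Kazakhstan has no allocation, so there the first MCQ comes before the VP case.
2. Analyse the post-education score by regression on arm and pre-allocation score, with heteroscedasticity-robust standard errors, in place of the unadjusted Welch test. This keeps the protection against unequal variances. At each correlation tabulated it also needs fewer patients than a change score.
3. In the multisite analysis add site. State that all-VP Kazakhstan then contributes almost nothing to the arm contrast (it only helps to estimate the baseline slope), and report it descriptively or as a sensitivity analysis.
4. Claim retention only if the second test follows a stated delay; otherwise call the outcome knowledge.

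The cost is one repeat of a short quiz, with a further contact if the test is delayed, and a regression instead of a t test. The instrument still has to be translated under the plan, and the repeat uses the same translation. Item 3 is a real change, because the article chose to include the Kazakh sample in the multisite comparison. Baseline adjustment corrects only for measured initial knowledge; it does not make the Ukrainian allocation random. The size of the precision gain depends on a correlation that the article does not give.

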### Inclusion and Exclusion Criteria and the Recruitment Process

The inclusion and exclusion criteria are outlined in Textbox 1. The dropout criterion is withdrawing consent during the study period.

In the Greek pilot where randomization of patient cohorts would occur, a simple coin toss algorithm will be used, implemented by Excel’s (Microsoft Corp) RANDBETWEEN function. This will allocate patients between the VP education cohort and the control (normal clinical information) cohort. In the Ukraine pilot, a sampling of convenience will allocate most of the participants to the VP cohorts and fewer to the control (normal clinical information) cohort. In the Kazakhstan pilot, all accepted patients will be allocated to the VP intervention cohort. While this decision by the medical team of this center makes impossible the conduct of a distinct local evaluation of impact, we chose to include the sample in the multicentric data processing part of the study. It should be noted that evaluation results will be extracted on a per-site basis only in the Greece and Ukraine arms of the study. In the multisite comparison, the whole sample of intervention patients (including the totality of the Kazakh cohort) will be compared to the totality of the sample of control patients from Greece and Ukraine cohorts.

Patients who meet the requirements for that study will be informed about the study and will be asked if they would like to participate in it. They will then sign the consent form to take part in the study. Patients who may withdraw their consent during the study will be excluded from the analysis.

Study inclusion and exclusion criteria.

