### Conclusions

This project can generate new knowledge and relevant results for a deployed VP regimen for the education and engagement of patients with AF on crucial topics regarding their condition. A 3-center pseudorandomized controlled trial could add data to the evidence regarding the effects of interventions using VP resources in outreach and training endeavors for empowering patients with AF.

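### Ukraine allocates patients to VP or control by convenience but keeps its own per-site evaluation beside randomised Greece, so its VP-control difference is open to selection bias of unknown size and direction

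*Protocol article*

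**What the plan says.** The section on inclusion criteria and recruitment sets a different allocation method for each site.

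- **Greece:** "a simple coin toss algorithm will be used, implemented by Excel’s (Microsoft Corp) RANDBETWEEN function".
- **Ukraine:** "a sampling of convenience will allocate most of the participants to the VP cohorts and fewer to the control" cohort. No ratio is given. Intervention Cohorts adds only this: "In Ukraine, 160 patients will be reached and will be divided into the control and intervention groups".
- **Kazakhstan:** "In the Kazakhstan pilot, all accepted patients will be allocated to the VP intervention cohort". The article accepts that this rules out a local evaluation of impact.

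On analysis, the same section states that "evaluation results will be extracted on a per-site basis only in the Greece and Ukraine arms of the study". Ukrainian patients also enter the multisite comparison, where "the whole sample of intervention patients (including the totality of the Kazakh cohort) will be compared to the totality of the sample of control patients". Efficacy is one of the primary outcomes under Study Design.

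The Welch t test is justified, under Intervention Cohorts and again under Results, by unequal group sizes and variances. Limitations names the unvalidated questionnaire and the lack of a qualitative exploration of acceptance. It does not name allocation.

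**The concern.** A per-site VP-control difference can be read as an effect of the VP only if the two groups would have scored alike under the same education. In Greece the random draw secures this in expectation. In Ukraine nothing does. Whatever makes a patient convenient for the app arm, such as age, schooling, digital skill, clinic day or staff availability, may also be related to the knowledge score.

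The article recognises that Kazakhstan cannot support a local evaluation because it has no controls. It applies no similar caution to Ukraine, which has controls but gives no reason to think them comparable. A reader would see two per-site results side by side, one randomised and one not, with nothing in the stated limitations to separate them. The Ukrainian patients also carry the same problem into the pooled comparison.

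**Working it through.** The article gives no alpha, power, effect size, SD or Ukrainian ratio, so there is no stated figure to reproduce. The point rests on the allocation rule. The arithmetic below only shows how sensitive a Ukrainian test would be.

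**Input from the article:** 160 patients reached in Ukraine (Intervention Cohorts). This is the number contacted, not the number analysed.

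**Assumptions not in the article:** two-sided alpha 0.05; equal SDs; normal approximation; no true VP effect; a 3:1 split to represent a mostly-VP allocation; a selection gap b of 0.2 to 0.5 SD in the knowledge the two groups would show without any VP effect.

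**Formulas, in SD units:**

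- SE = √(1/n_VP + 1/n_control)
- False-positive rate = Φ(b/SE − 1.96) + Φ(−b/SE − 1.96)

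**All 160 analysed, 120 VP and 40 control:** SE = √(1/120 + 1/40) = 0.183. For b = 0.3, b/SE = 0.3/0.1826 = 1.643. The rate is Φ(−0.317) + Φ(−3.603) = 0.376.

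**Half analysed, 60 VP and 20 control:** SE = √(1/60 + 1/20) = 0.258. For b = 0.3, b/SE = 1.162. The rate is Φ(−0.798) + Φ(−3.122) = 0.213.

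| Split (VP/control) | b = 0 | b = 0.2 | b = 0.3 | b = 0.5 |
|---|---|---|---|---|
| 107/53 (about 2:1) | 5% | 22.2% | 43.1% | 84.5% |
| 120/40 (3:1) | 5% | 19.5% | 37.6% | 78.2% |
| 128/32 (4:1) | 5% | 17.3% | 32.9% | 71.6% |
| 60/20 (3:1, half analysed) | 5% | 12.1% | 21.3% | 49.1% |

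A larger sample makes the error rate worse, because the gap b stays while SE shrinks. The Welch correction changes the SE and the degrees of freedom. It leaves b in the difference of means.

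**Allocation text compared.** Study Design says that the core sample will be recruited by the process used in the prepilot arm, and that process included random allocation of half the patients to each cohort. The recruitment section then gives Ukraine convenience allocation. The first statement is about recruiting, so this is a tension rather than a flat contradiction, but the two passages should be reconciled.

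**The case against.** The strongest reply is that the article is open about this. It calls the trial pseudorandomised, confines randomisation to Greece and states Ukraine's method plainly. A reader might infer that it passes Ukraine off as randomised; it does not. That much stands. But one label covers a randomised site, a convenience site and a single-arm site, and no caveat is attached to the Ukrainian result.

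Three stronger readings are tempting and not supported.

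- **That unblinded clinicians choose who gets the app.** The article does not say who assigns patients or on what basis. On masking it says only that "Participants and trial personnel will not be blinded after the point of assignment to interventions".
- **That the bias must favour the VP.** This is plausible, since patients who take easily to an app may also do well on a quiz. It remains an inference. Internet access and adequate equipment are required of every participant, which narrows differences in digital ability, and convenience could mean something as neutral as clinic day.
- **That the Ukrainian comparison is fixed as unadjusted.** Results names the Welch test for the prepilot questionnaires, and Intervention Cohorts links it to the multicentre cohort. No model is specified for the Ukrainian per-site comparison, and an analysis plan that is not shown may adjust. Adjustment could deal with measured differences but could not supply the comparability that randomisation gives.

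It is also fair to say that the Greek comparison is randomised, is reported separately and is untouched by this.

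**Conclusion.** The point holds for the Ukrainian per-site result. Followed as written, the plan produces a comparison whose difference cannot be attributed to the VP, with bias of unknown size and direction that the named test does not address and the Limitations do not mention.

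The figures of about 38% (all 160 analysed) and 21% (half analysed) at a 0.3 SD gap are illustrations. They depend on an assumed alpha, split and gap, and do not measure the bias in this trial. The finding does not depend on them.

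A reader might also infer that randomising Ukraine would rescue the pooled comparison. It would not, because Kazakhstan contributes VP patients and no controls.

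**What to change.** **Preferred.** Before Ukrainian enrolment starts, replace convenience allocation with randomisation of consenting patients at a fixed unequal ratio, for example 2:1 or 3:1 in favour of the VP. The article gives no reason against this, and it keeps the mostly-VP split. At 3:1, 160 enrolled patients would give about 120 and 40. Use a concealed, logged list or a central draw. An open RANDBETWEEN sheet recalculates and can be redrawn, so copying the Greek tool unchanged is not enough. Reconcile the Study Design statement about following the prepilot process with the site-specific allocation rules.

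**If the site will not randomise.**

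- Label the Ukrainian result a non-randomised comparison and report it separately from the Greek randomised estimate.
- Confirm that the quiz is given there before allocation, and adjust for it. A quiz before allocation is clearly described only for Greece.
- Make no per-site efficacy claim from Ukraine.
- Add non-random allocation to the Limitations.

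**Cost.** A short protocol change and an allocation list for one site, with no extra patients. The site loses discretion over assignment and must agree to that, which cannot be presumed given that the Kazakh medical team set its own allocation. Randomising removes systematic selection at assignment. It does not remove the effects of unblinded delivery or of excluding patients who withdraw consent, and it leaves the pooled comparison unrepaired.

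### Ukraine is planned with more VP than control patients, with no ratio or reason given, and the Welch test does not recover the precision that a small control arm costs

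*Protocol article*

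**What the plan says.** All references are to the protocol article.

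- **Allocation in Ukraine** (Inclusion and Exclusion Criteria and the Recruitment Process): "a sampling of convenience will allocate most of the participants to the VP cohorts and fewer to the control (normal clinical information) cohort". No ratio and no reason are given. In Greece, by contrast, a spreadsheet coin toss is used, and half of the patients go to each arm. In Kazakhstan every accepted patient goes to VP.
- **Comparisons** (same section): "evaluation results will be extracted on a per-site basis only in the Greece and Ukraine arms of the study". The multisite comparison sets all VP patients, Kazakhs included, against the Greek and Ukrainian controls.
- **Numbers** (Intervention Cohorts): "In Ukraine, 160 patients will be reached and will be divided into the control and intervention groups"; "In Greece, a pool of 700 patients will be reached by phone, and they will participate in the trial from their home"; "Finally, at the Kazakhstan center, 190 patients will be contacted". These are patients approached, so they are upper limits on patients analysed.
- **Adequacy** (Intervention Cohorts): "sufficient sample sizes for control and intervention groups will be ensured". No figure is attached.
- **Response to unequal arms**: the Welch t test, "which is robust to large sample size inequalities" (Intervention Cohorts). The Results section, in a paragraph that opens with the prepilot questionnaires, explains that the test does not assume equal variances and concludes that it "is robust to widely varying sample sizes".

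**The concern.** The point here is the allocation ratio; how patients are chosen for each arm is a separate and larger matter. The precision of a difference between two means is governed mainly by the smaller arm. Controls are the scarce group in this trial, because one of the three sites contributes none. Ukraine is one of only two sites with its own efficacy result, and its plan thins exactly that group.

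The Welch test is the only answer the article offers to unequal arms. It deals with the validity of the test under unequal variances, which is a different matter from how wide the interval will be. At stake is a wider interval and lower power for the Ukrainian comparison, and fewer controls for the pooled one.

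**Working it through.** The article states no ratio, alpha, power, effect size or standard deviation (SD), so it has no figure of its own to reproduce. What follows shows the size over a range of assumed ratios.

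**Inputs.** From the article: at most 160 patients in Ukraine, a pool of 700 in Greece split in half, and 190 in Kazakhstan, all VP. Assumed: ratios from 3:2 to 4:1, two-sided 5% test, and an effect of 0.5 SD for the power column.

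**Step 1. Effective sample with equal SDs.** The variance of the difference is proportional to 1/n1 + 1/n2. The size of an equally split sample with the same precision is 4·n1·n2/(n1 + n2). For 3:1 this is 4 × 120 × 40 / 160 = 120, a loss of 1 − 120/160 = 25%. The interval widens by √(160/120) = 1.15. Power is from the noncentral t distribution.

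| VP:control | Patients | Effective N | Loss | Interval width | Power at 0.5 SD |
|---|---|---|---|---|---|
| 1:1 | 80:80 | 160 | 0% | 1.00 | 88% |
| 3:2 | 96:64 | 153.6 | 4% | 1.02 | 87% |
| 2:1 | 107:53 | 141.8 | 11% | 1.06 | 84% |
| 3:1 | 120:40 | 120 | 25% | 1.15 | 78% |
| 4:1 | 128:32 | 102.4 | 36% | 1.25 | 71% |

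If only 80 take part, power is 60% at 1:1, 48% at 3:1 and 42% at 4:1. The Welch statistic uses the same two arm sizes, so it inherits these losses.

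**Step 2. Unequal SDs.** With p the VP share and r = SD in VP / SD in control, the loss against 1:1 is 1 − (2r² + 2)/(r²/p + 1/(1 − p)). For r = 1.5 and p = 2/3 this is 1 − 6.5/6.375 = −2%, a small gain.

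| r | 2:1 | 3:1 | 4:1 |
|---|---|---|---|
| 0.67 | 21% | 37% | 48% |
| 1 | 11% | 25% | 36% |
| 1.5 | −2% | 7% | 17% |
| 2 | −11% | −7% | 0% |

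**Step 3. Is Ukraine the smaller site comparison?** If all 160 take part, it is smaller than Greece once Greek participation exceeds 160/700 = 22.9%. The Greek response rate is not given.

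**Step 4. The pooled comparison.** If everyone approached takes part and Ukraine is 1:1, the VP arm is 350 + 80 + 190 = 620 and the control arm 350 + 80 = 430. At 3:1 in Ukraine they are 660 and 390. The loss is 1 − (660 × 390)/(620 × 430) = 3%. If 30% of the Greek pool takes part (105 per arm), the arms are 375 and 185 at 1:1, or 415 and 145 at 3:1. The loss is then 1 − (415 × 145)/(375 × 185) = 13%.

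**The case against.** Several stronger readings are tempting, and the article does not support them.

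- **That Ukraine loses 11% to 36%.** Those figures are 2:1 and 4:1 with equal SDs. The article says only that VP gets more, which also fits 3:2 and a loss of 4%. The Welch test was chosen so as not to assume equal variances, and if VP scores vary enough more than control scores the loss vanishes or reverses. This objection stands, so the figures can only be given as a conditional range.
- **That the plan claims Welch restores power.** It does not mention power. Its stated reasons are unequal variances and not discarding VP data. Calling the test robust to sample size differences is loose wording, no more.
- **That the Ukrainian comparison is underpowered.** With no effect size or power target, this cannot be shown. The 0.5 SD above is illustrative.
- **That Welch's error rate breaks down.** Simulations of ten logistic items with assumed mean scores of 26 to 35 out of 38 gave 5.1% to 6.5% at 64:16. No score distribution is given in the article, so this is not part of the finding.
- **That the imbalance brings nothing.** Acceptance is listed among the primary outcomes under Study Design, and more VP patients give more acceptance data. This stands as a real, if small, return.

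The remaining objection is that convenience allocation is the bigger defect and that a 1:1 split by convenience would not cure it. That is right, and the fix takes it up. The ratio still matters separately, because patients can be randomised at any ratio.

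**Conclusion.** The point holds in conditional form. The article deliberately plans fewer controls than VP patients in Ukraine, without a ratio or a reason. Ukraine has its own comparison, probably smaller than the Greek one, and another site already supplies no controls. The Welch test leaves the resulting loss of precision untouched. That loss runs from 4% at 3:2 to 36% at 4:1, provided the SDs are equal. It grows if VP scores vary less than control scores, as might happen if they crowd towards the maximum score, and shrinks or disappears if they vary more. In the pooled comparison a 3:1 split in Ukraine costs about 3% with full participation and about 13% if 30% of the Greek pool takes part. This is worth changing because the remedy is cheap.

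**What to change.** In the recruitment section and in Intervention Cohorts, replace the Ukrainian allocation sentences with, for example: *In Ukraine, consenting patients will be allocated at random in a 1:1 ratio to the VP and control cohorts, by the procedure used in Greece.* If local constraints rule out 1:1, state the planned ratio and the reason for it.

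Random allocation is the preferred half of this change. A 1:1 convenience split would narrow the interval around a comparison still open to selection bias. A coin toss will not give exactly 80:80, but this matters little: the SD of the VP count is √(160 × 0.25) = 6.3, and a departure of two SDs costs (12.6/80)² = 2.5% of effective sample.

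Rewording the Welch sentences, to say that the test guards against unequal variances and does not offset a small arm, is optional.

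No extra patients are needed. The cost is about 80 Ukrainian VP acceptance responses instead of 107 to 128 (2:1 to 4:1) if all 160 take part. Against 3:1 that is 40 fewer of up to 660 across sites, partly offset by the all-VP Kazakh cohort. The article does not say why Ukraine planned fewer controls, so the site should confirm that equal allocation is feasible.
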